## Abstract

**Background:** High systolic blood pressure (BP) is associated with an increased risk of intracranial hemorrhage (ICH) in patients undergoing reperfusion therapy. However, there are no data from randomized trials to guide BP management after reperfusion following endovascular therapy (EVT) for patients with acute ischemic stroke (AIS) with large vessel occlusion (LVO). The objective is to evaluate if BP control with a target of 100–129 mmHg systolic BP (“tight” SBP control) can reduce ICH as compared to 130–185 mmHg (“usual” SBP control) in AIS participants after reperfusion by EVT.

**Methods:** The BP TARGET trial is a multicenter, prospective, randomized, controlled, open-label, blinded endpoint clinical trial. AIS participants with LVO experiencing successful reperfusion are randomly assigned, in a 1:1 ratio, to have a “tight” SBP control (100–129 mmHg) or a conservative SBP control (130–185 mmHg) during the following 24–36 h. The primary outcome is the rate of ICH (either symptomatic or asymptomatic) on follow-up CT scan at 24–36 h. Secondary outcomes include the rate of the symptomatic ICH, the overall distribution of the modified Rankin Scale (mRS) at 90 days, favorable outcome (90–day mRs 0–2), infarct volume at follow-up CT scan at 24–36 h, change in National Institute of Health Stroke Scale at 24 h, and all-cause mortality at 90 days.

**Conclusion:** This is the first randomized trial directly comparing the efficacy of different SBP targets after EVT reperfusion. This prospective trial aims to determine whether a “tight” SBP control after EVT reperfusion can reduce the risk of ICH.

## Introduction and Rationale

High blood pressure (BP) in the setting of acute ischemic stroke (AIS), defined by a systolic BP (SBP) >140 mmHg and diastolic BP (DBP) >90 mmHg (1, 2), occurs in up to 50% of patients and is a predictor of unfavorable outcome (3–5). High BP is associated with an increased risk of intracranial hemorrhage (ICH) in AIS patients treated with alteplase (6). In patients eligible for reperfusion therapies, such as alteplase, BP should be below 185/110 mmHg prior to initiation of therapy (7). In the Safe Implementation of Thrombolysis in Stroke-MOnitoring STudy (SITS-MOST) registry, SBP had a linear relationship with the ICH risk (i.e., the risk increases for high SBP values) (6). High BP values also seem to contribute to the prognosis of AIS patients with large vessel occlusions (LVO) of the anterior circulation treated with endovascular therapy (EVT). Available evidence, in EVT-treated patients, shows that mortality increases for lower and higher baseline SBP values following a U-shaped relationship (8), with a nadir at 157 mmHg (9). In addition, higher SBP peak values independently correlate with unfavorable outcome and a higher ICH rate within 48 h after EVT (8–13). Despite high reperfusion rates and a strong benefit of EVT, more than 50% of patients will remain disabled (14). The lack of clinical recovery may be a consequence, at least in part, of reperfusion injuries including ICH.

Current international guidelines do not discriminate BP management between patients treated with IVT alone and patients treated with EVT and IVT and propose the same BP threshold. Recently, a substantial number of observational studies have begun to shed light on the association between higher post-EVT BP values (SBP >140 or 160 mmHg) and ICH or worse functional outcomes according to the recanalization score (i.e., TICI < 2B vs. TICI ≥ 2B), but with conflicting results (12, 13). Given the lack of data from a randomized controlled trial, an online survey regarding post-EVT BP management was performed across institutions in the United States (StrokeNet Sites)(15). In recanalized patients after EVT, most institutions (36%) seemed to target an SBP in the range of 120–139 mmHg and allow permissive hypertension in nonrecanalized patients.

Taken together, these data underline the need of a randomized controlled trial assessing different BP targets after EVT reperfusion. The BP TARGET trial aims to assess the efficacy of a “tight” BP lowering control (with a target 100–129 mmHg for SBP) versus a more conservative BP control (SBP 130–185 mmHg) following 24 h after reperfusion by EVT in AIS patients.

## Methods

### Design

BP TARGET is a prospective, randomized, multicenter, controlled, open-label, with blinded endpoint design (PROBE). This trial, funded by the French government, is conducted in four high-volume comprehensive stroke centers in France.

Enrollment into the BP TARGET study started in June 2017 and is projected to be completed by December 2019. The data collection phase of study is expected to be completed by January 2020. The study, which is registered with ClinicalTrials.gov (ClinicalTrials.gov Identifier: NCT03160677), is conducted in accordance with the Declaration of Helsinki and Good Clinical Practice. Research ethics approval was obtained from the Comité de Protection des Personnes Sud Méditerranée IV on March 14, 2017. Data collection during the study is reported in Table 1 and carried out using an electronic case report form (eCRF), developed using Cleanfile® software.

**Table 1 T1:** Data collection during the study.

	**Inclusion**	**24-h follow-up**	**72-h follow-up**	**3-month follow-up**
Eligibility criteria	✓			
Informed Consent	✓			
Randomization	✓			
Clinical examination	✓			
mRS score	✓			✓^1^
NIHSS score	✓	✓		
Concomitant Medications	✓	✓		✓
CT scan		✓	✓^2^	
Adverse Event assessment		✓		✓

1 *Must be completed by a BLINDED stroke study team member. CT/CTA or MRI/MRA are required at baseline, and any time there is a neurological deterioration (a change in NIHSS of 4 points or more) or hemorrhage*.

2 *Performed if CT at 24 hours shows a hyperdensity. CT, computed tomography, mRS, modified Rankin Scale; NIHSS, National Institute of Health Stroke Scale*.

### Patient Population

Eligible participants have an AIS due to a large vessel occlusion (LVO) of the anterior circulation [i.e., internal carotid and/or proximal middle cerebral artery (M1) occlusions] and have reperfusion by EVT defined as modified Thrombolysis In Cerebral Infarction (mTICI) of 2b or 3.

### Baseline Eligibility Evaluation

A written consent form must be signed by the participant or legal representative before randomization. Emergency consent procedure may be considered if consent by the participant or a proxy is not possible. In this situation, the participant's consent confirmation is still required and gathered when the participant is able to consent by him- or herself. Reperfusion will be evaluated at the end of the procedure and defined by an mTICI of 2b or 3. For eligibility, SBP needs to be over 130 mmHg during the hour following the intervention. Detailed inclusion and exclusion criteria are in Table 2.

**Table 2 T2:** Inclusion and exclusion criteria.

**Inclusion**	**Exclusion**
• Age 18 and older • Clinical diagnosis of AIS in the anterior circulation • Neuroimaging demonstrates large vessel proximal occlusion (ICA and/or MCA -M1) • With or without IV thrombolysis • Consenting requirements met according to French laws	• Acute ischemic stroke involving posterior circulation (vertebrobasilar occlusion) • Allergy to radiographic contrast agents. • Disability prior to the stroke (mRS >3) • Pregnant or breastfeeding women • Severe or fatal comorbidities that will likely prevent improvement or follow-up or that will render the procedure unlikely to benefit the patient • Under legal protection • No affiliation to a social security scheme • Opposition of the patient or their family

*ICA, internal carotid artery; IV, intravenous; MCA, middle cerebral artery; mRS, modified Rankin Scale*.

### Randomization

During the first hour following reperfusion, participants will be randomly allocated in a one-to-one ratio to a “tight” BP control, defined as a target SBP between 100 and 129 mmHg (experimental arm), or a standard BP control, defined as target SBP level between 130 and 185 mmHg (control arm), during the following 24 h (Figure 1). The randomization sequence will be provided by an independent statistician (who did not take part in assessing the participants at any point in the study) using computer-generated random numbers with block sizes of four and stratification by center and IV alteplase therapy use prior to EVT. The block size information is not specified in the protocol to ensure that vascular neurologists and interventional neuroradiologists will be not able to anticipate treatment arm assignment. The randomization sequence is implemented in the eCRF system to ensure a centralized real-time randomization procedure. Participants are enrolled and randomized by vascular neurologists or interventional neuroradiologists.

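### The public article discloses the fixed block size of four while enrolment is described as ongoing, which undoes the plan's own safeguard for patients randomised after disclosure

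*Protocol article*

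**What the plan says.** The Randomization section of the protocol article gives the method as "using computer-generated random numbers with block sizes of four and stratification by center and IV alteplase therapy use prior to EVT", and states that "participants will be randomly allocated in a one-to-one ratio". No second or varying block length is mentioned. The next sentence explains a precaution: "The block size information is not specified in the protocol to ensure that vascular neurologists and interventional neuroradiologists will be not able to anticipate" the treatment assignment. The same section then says "Participants are enrolled and randomized by vascular neurologists or interventional neuroradiologists", so the two specialties to be kept unaware of the block size are the ones who bring patients in. Delivery is central: "The randomization sequence is implemented in the eCRF system to ensure a centralized real-time randomization procedure".

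The Design section describes an open-label trial with blinded endpoint assessment that "is conducted in four high-volume comprehensive stroke centers in France". On timing it says: "Enrollment into the BP TARGET study started in June 2017 and is projected to be completed by December 2019".

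**The concern.** Keeping the block size secret is the only safeguard against prediction from past assignments that the article describes, and the article itself removes it. Once the size is known, central allocation through the eCRF still hides the list, but it does not stop anyone reconstructing it. Past assignments are visible because treatment is open-label and the arms differ by blood pressure target. The strata are also known, and each centre has only two of them.

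The risk is selection at enrolment. Randomisation takes place in the hour after reperfusion, when the angiographic result and the first post-procedure pressures are known. Eligibility leaves some room for judgement, for example on severe comorbidity and on the consent route (Baseline Eligibility Evaluation and Table 2). A physician who expects a particular arm could decide not to enrol a patient thought unsuited to it. Blinded CT reading protects the assessment of outcome, not the make-up of the arms. The primary model adjusts only for centre and alteplase (Statistical Analyses, Primary Outcome), so it would not correct an imbalance in other prognostic factors.

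**Working it through.** **Inputs from the article.** One block size of 4, allocation 1:1, strata of centre by alteplase (Randomization); 4 centres, hence 4 × 2 = 8 strata (Design); 320 patients planned (Sample Size Estimates). The article gives no figure for predictability, so only the total can be checked against a stated figure. For 40% versus 25%, two-sided 0.05 and 80% power, the pooled-variance formula without continuity correction gives 152 per arm, and 152/0.95 = 160 per arm, or 320. The article's total is reproduced.

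**Assignments known with certainty.** A 1:1 block of four has 6 equally likely sequences. The next assignment is certain once one arm has used both its places.

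- AABB and BBAA: positions 3 and 4 are certain, 2 × 2 = 4.
- The other four sequences: only position 4 is certain, 4 × 1 = 4.
- Total: 8 of 6 × 4 = 24 positions, 8/24 = 33.3%.

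The other two thirds stay uncertain even to someone with perfect knowledge of the past.

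**Best guess, always naming the arm that is behind.** The chance of being right at each position is:

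- Position 1: 1/2.
- Position 2: 2/3.
- Position 3: (1/3) × 1 + (2/3) × (1/2) = 2/3.
- Position 4: 1.

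The mean is (1/2 + 2/3 + 2/3 + 1)/4 = 17/24 = 70.8%, against 50% without this knowledge.

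**Incomplete last blocks.** Simulating 320 patients over 8 strata of equal expected size (an assumption) gives a mean of 32.3% certain, ranging from 28% to 37% across simulated trials. Unfinished blocks hardly change the figure.

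**How much of the trial is exposed.** The publication date is not in the document. For illustration, assume even accrual of 320 patients over about 30 months (June 2017 to December 2019), or 320/30 = 10.7 per month. Complete tracking of every stratum is also assumed.

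| Months of enrolment left at disclosure | Patients exposed | Certain at most (exposed/3) | Share of 320 |
|---|---|---|---|
| 0 | 0 | 0 | 0% |
| 3 | 32 | 11 | 3% |
| 6 | 64 | 21 | 7% |

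**What this could do to the estimate.** Suppose steering made the underlying ICH risk differ by 10 points between allocations known to be tight and those known to be control (an assumption; the article offers no figure). Counting only certain allocations, the bias among exposed patients would be about 10 × 1/3 = 3.3 points. Over the whole trial it would be 3.3 × 32/320 = 0.3 points in the 3-month case and 3.3 × 64/320 = 0.7 points in the 6-month case. The planned difference is 15 points.

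**Other fixed sizes.** If the size is known, the certain share is 1/4 for blocks of six and 1/5 for blocks of eight. A larger fixed block that is also published lessens the problem without removing it.

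**The case against.** The secrecy sentence speaks of the protocol, and this document is an article about it. Both statements can be true together: the full protocol may be silent on block size, and nothing shows that any site document contained it. This stands. A reader might infer that the design contradicts itself, but the documents show only a disclosure through publication that works against the precaution.

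A reader might also infer that one third of this trial's allocations were knowable in advance. The documents do not support that. Disclosure can affect only patients randomised after it, and the exposed share could be none. Certainty also requires knowing where the current block starts, which means a complete ordered record of one centre-by-alteplase stratum. With two enrolling specialties and central allocation, no document shows that anyone holds such a record. The 33% and 71% are therefore ceilings.

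Randomising within an hour of reperfusion leaves little room to wait for a preferred allocation. This weakens the concern about timing, but not about leaving a patient out. The independent statistician, central allocation and blinded core-laboratory reading all remain in place, though none prevents prediction from past open assignments once the block size is known.

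Finally, withdrawing the phrase from the article would not undo the disclosure. This is correct, and the fix does not rely on it.

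**Conclusion.** The point holds in a limited form. The article makes public a fixed, small block size that the plan deliberately withheld from the physicians who enrol, and its own wording places this during enrolment. For patients randomised after disclosure, at most 33% of allocations could be known with certainty and guesses could be right at most 71% of the time. Both figures assume full tracking of assignment order within a stratum and knowledge of block starts.

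The figures do not extend to all 320 patients. The overlap between disclosure and enrolment rests only on the statement that completion was projected for December 2019, and its length is unknown. A reader might conclude that selection bias occurred; nothing in the document shows that any assignment was predicted or any patient held back. The sample size is unaffected. This is a should-fix matter: a real and avoidable risk of uncertain, possibly small, extent.

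**What to change.** **Allocations not yet made.** The independent statistician replaces the unused part of the list in every stratum with randomly varying block lengths, and keeps the lengths out of every public or site document until enrolment closes. Certainty then disappears for anyone who does not know the lengths, although guessing towards balance will still do somewhat better than 50%.

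**Patients randomised after disclosure.** Add a sensitivity check. Using allocation order, stratum and the known block size, classify each such allocation as predictable as tight or predictable as control according to which arm was behind in its block. Compare baseline NIHSS, age and pre-randomisation SBP between the two classes. Without steering, the classes should differ only by chance. The cut-off should be the earliest date on which anyone at an enrolling site could have learned the block size. With few exposed patients the check will have little power, so report estimates with intervals and do not rely on a test alone.

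**Cost.** One documented reload of a live eCRF system, and some truncated blocks in up to eight strata. A block of four cut short leaves an imbalance of at most 2, so at most 8 × 2 = 16 overall in the unlikely case that all lean the same way. Patients already randomised are not affected. If enrolment has closed, only the sensitivity check applies, and it needs no data beyond those already collected.

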**Figure 1 F1:**
[figure not shown]
Patient flow diagram.

### Interventions

Once the subject is randomized, the BP target has to be obtained within 1 h.

#### Experimental Arm: Target SBP 100–129 mmHg

Participants allocated to this arm will achieve an SBP target of 100–129 mmHg during the following 24 h. BP measurement is performed with automatic sphygmomanometers and conducted for 24 h, based on the guidelines (16), as follows: every 15 min for 2 h from the start of alteplase therapy, then every 30 min for 6 h, and then every hour for the remaining 16 h. Investigators are free to choose antihypertensive medications to achieve the target BP based on their current practice.

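### The only stated blood pressure reading schedule starts at alteplase, but the assigned SBP target runs for 24 h from randomisation after EVT

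*Protocol article*

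**What the plan says.** **Reading schedule.** The experimental-arm section asks for automatic cuff readings over 24 h: "every 15 min for 2 h from the start of alteplase therapy, then every 30 min for 6 h", and then hourly for the last 16 h. The control-arm section adopts the same procedure. No other schedule and no other origin is given.

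**Target window.** The Randomization section states: "During the first hour following reperfusion, participants will be randomly allocated in a one-to-one ratio". The control target is a "target SBP level between 130 and 185 mmHg (control arm), during the following 24 h", and the experimental target covers the same period. The Interventions section adds: "Once the subject is randomized, the BP target has to be obtained within 1 h".

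**Alteplase.** Table 2 admits patients "With or without IV thrombolysis". Randomisation uses "stratification by center and IV alteplase therapy use prior to EVT", so patients without alteplase form a planned stratum, and alteplase, where given, comes before EVT.

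**Other wordings of the window.** The Introduction refers to the "following 24 h after reperfusion by EVT in AIS patients", and the sample size section also counts 24 h from reperfusion. The Abstract instead has "a conservative SBP control (130–185 mmHg) during the following 24–36 h".

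**Where SBP is used.** The feasibility outcome is the proportion of experimental patients whose mean SBP during management is below 130 mmHg. The per-protocol population drops patients who did not reach their assigned target.

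**The concern.** The schedule and the intervention run on different clocks. The treatment under test is a blood pressure level held for 24 h after randomisation, so readings in those 24 h are the evidence that it was delivered. A schedule that starts at alteplase begins before randomisation, and it cannot start at all in a patient who received none.

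Three things are at stake:

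- whether scheduled readings are dense during titration, when SBP is being brought to target within 1 h;
- whether scheduled readings continue to the end of the target window;
- whether mean SBP and target achievement are computed over the same period in both alteplase strata. A mean taken over the schedule as written would mix readings from before assignment with readings under the assigned target.

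**Working it through.** **1. The article's own figures.** The schedule lasts 2 + 6 + 16 = 24 h, which agrees with the stated 24 h of measurement. Counting one reading at the end of each interval gives 120/15 + 360/30 + 16 = 8 + 12 + 16 = 36 readings. A reading at time zero would make 37.

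**2. Order of events.** Alteplase comes before EVT, EVT before reperfusion, and reperfusion at most 1 h before randomisation. The target window starts at randomisation. The delay D from alteplase to randomisation is therefore above zero. The article does not give it, so I assume 1 to 5 h.

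**3. Patients without alteplase.** D is undefined. The text gives no time at which their 15-min phase begins.

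**4. Patients with alteplase.** The schedule ends 24 h after alteplase, and the window ends D + 24 h after alteplase.

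- Time without a scheduled reading: (D + 24) − 24 = D hours, a share of D/24.
- Readings in the window: scheduled times t with D < t ≤ D + 24.
- Early readings: the same count for the first 1 h and first 2 h after randomisation.

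| D (assumed) | Window without scheduled reading | Readings in window | In first 1 h | In first 2 h |
|---|---|---|---|---|
| 0 (start at randomisation) | 0 h (0%) | 36 | 4 | 8 |
| 1 h | 1 h (4.2%) | 32 | 4 | 6 |
| 2 h | 2 h (8.3%) | 28 | 2 | 4 |
| 3 h | 3 h (12.5%) | 26 | 2 | 4 |
| 4 h | 4 h (16.7%) | 24 | 2 | 4 |
| 5 h | 5 h (20.8%) | 22 | 2 | 4 |

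The 15-min phase has max(0, 2 − D) hours left at randomisation: 1 h for D = 1 h, none from D = 2 h. The loss against the first row is 4, 8, 10, 12 and 14 readings. It is the same if time zero is counted (33, 29, 27, 25 and 23 of 37 remain).

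**5. Window counted from reperfusion.** Randomisation follows within 1 h, so each gap shrinks by at most 1 h.

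**6. Sample size.** For 40% against 25%, two-sided 5% and 80% power, with a mean proportion of 0.325:

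n = [1.960·√(2 × 0.325 × 0.675) + 0.842·√(0.40 × 0.60 + 0.25 × 0.75)]² / 0.15² ≈ 152 per arm, and 304/0.95 = 320 in total.

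Both match the article, and neither uses a blood pressure reading.

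**7. What a repaired schedule does to a mean.** Started at randomisation, it puts 8 of 36 readings (22%) in the first 2 h, which are 2/24 (8%) of the time. Without the first hour, 32 readings remain over 23 h, of which 16 (50%) fall in hours 1 to 8, or 7/23 (30%) of that time. A plain average of readings would still overweight the early period.

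**The case against.** **The literal reading is implausible.** The schedule stands inside the description of an arm that exists only after randomisation, it lasts as long as the target window, and the 1 h limit for reaching target implies readings from randomisation. The text cites guidelines for the schedule, so the anchor is probably thrombolysis wording carried over. This stands as the likely cause. It does not correct the rule: the only origin stated is wrong for the window and empty for one stratum.

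**The full protocol may give the bedside detail.** That would excuse silence. Here the article names an origin, and the origin does not fit.

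**Four stronger readings are tempting, and none is supported.**

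- *Readings were missing late in the window.* The article shows only what was scheduled. Staff holding a target may well have gone on measuring.
- *The feasibility outcome or per-protocol set is wrong.* The mean is defined over the management period, the per-protocol rule names no source of readings, and nothing says that scheduled readings alone supply these data. Nor is detection of hypotensive events tied to the schedule.
- *The arms are compared unfairly.* Both share one schedule.
- *A third or more of the window is uncovered.* That needs the Abstract's upper limit of 36 h. Even a schedule started at randomisation would then leave 12/36 (33%) without readings, so this is a separate inconsistency. The Methods give 24 h throughout.

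**Conclusion.** The point holds as a minor error in a stated operating rule. Two consequences follow from the text alone, if it is read literally: patients without alteplase have no schedule origin, and in alteplase patients the schedule ends before the target window by the alteplase-to-randomisation delay. The sizes (4% to 21% of the window without a scheduled reading, and half the early readings from a 2 h delay) rest on the assumed 1 to 5 h and on that literal reading. They illustrate the mismatch and do not estimate data lost. Neither the primary intention-to-treat comparison nor the planned 320 patients is affected, and no patient's mean SBP or per-protocol status is shown to change.

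**What to change.** 1. In the experimental-arm section, make randomisation the origin of the schedule for all participants, with or without alteplase. The control-arm section then inherits it.
2. Derive mean SBP and target achievement from post-randomisation readings only, from the end of the 1 h allowed to reach target until 24 h after randomisation, identically in both arms and both strata. Use a time-weighted mean so that the denser early readings do not dominate.
3. Separately, bring the Abstract's period of SBP control into line with the 24 h in the Methods.

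The cost is a wording change and a reminder to sites. Alteplase patients would have about 4 to 14 more scheduled cuff readings after randomisation, for an assumed delay of 1 to 5 h. No patients, visits or scans are added. Enrolment began in June 2017, so for patients already treated only the analysis window in step 2 can still be set.
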